## Methodology

### Design

This observational study will involve three steps; Step 1) Recruitment, Step 2) Laboratory assessment of People with suspected PD, confirmed PD and healthy controls, Step 3a) home assessment of people with confirmed PD, and step 3b) re-test home assessment of people with confirmed PD. Participants do not have to be involved in all steps of the study to be recruited (i.e., they could do only the lab or the home assessment, or both). * in ‘OFF’ and ‘ON’ states.

### Study setting

Due to the non-invasive nature and short reading time required for the OMT measurement, data can be collected at the Clinical Gait Laboratory in Northumbria University, and within the participant’s home. For data collection for ON/OFF medication states, data will be collected in the participants’ home. This minimises the time for which the participant needs to be OFF their medication and reduces risks associated with travelling to the lab in their OFF state.

### Ethical approval and trial registration

A Northumbria University research ethics committee granted ethical approval (Project No. 0034). The trial has been reviewed and registered with Clinicaltrials.gov (NCT06051877). This study also received NHS REC approval (REF: 23/WM/0004), and MHRA letter of no objection (REF: CI/2023/0031/GB). Recruitment began 10^th^ of June 2023.

### Participants

#### Step 1) Recruitment

Participants will be a volunteer sample recruited from Northumbria Healthcare NHS foundation Trust. Participants will be seen in clinic by a Movements Disorders specialist at these sites where people are referred for suspected PD diagnosis, and those with diagnosed PD will be identified. Potential participants will be invited to consider the study and referred to the investigators who will attend the clinics. Healthy controls could include spouses/ siblings/ other volunteer older adults. We will recruit healthy older adults from advertisement using posters, which will be placed within neurology and geriatric departments. We will also recruit older adult and PD participants from previous or ongoing studies at Northumbria University where the participant has given written informed consent to be contacted regarding future research studies, and from local PD support groups.

*Inclusion / Exclusion criteria*. PD participants will be included if they have a diagnosis of PD according to UK brain bank criteria. PD and older adult participants will be excluded if there is any psychiatric co-morbidity, a history or evidence of head injury or ocular disease (such as cataracts), they have a clinical diagnosis of dementia or other severe cognitive impairment (measured using the MoCA with a cut off score of <21). For those involved in Step 3 of the project, PD participants must be consistently taking dopaminergic (‘anti-Parkinson’s’) medication.

#### Step 2) Lab assessment

We will recruit 30 confirmed PD, 30 suspected PD, and 30 age-matched healthy control participants for laboratory and home-based assessment of OMT (Fig 1). As this is a pilot study of a novel OMT measurement device and we are interested in the feasibility of measuring OMT in a real-world clinic setting rather than determining efficacy of OMT for differential diagnostics in PD within clinical settings, a formal sample size calculation was not conducted. We have based the sample size on previous studies of eye-tracking in PD that have used samples <30 per group and found significant differences compared to controls [34].

**Fig 1 pone.0313452.g001:**
[figure not shown]
SPIRIT diagram, schedule of enrolment and assessments.

#### Step 3a) Home assessment 1

We will recruit 30 people with confirmed PD to participate in a home based assessment.

#### Step 3b) Home assessment 2

We will recruit 20 people with confirmed PD who participated in step 3a to participate in a second re-test home based assessment of reliability.

### Equipment

#### iTremor (see Fig 2)

A portable, handheld device that uses optical sensors to measure OMT, a method based on measuring angular displacement using laser speckle correlation of images recorded in the Fourier plane of a lens [35]. This method is able to detect OMT frequency regardless of other eye movements, head movements and tear flow [36]. The iTremor device captures 500 frames per second, at a resolution of 2 mrad and a dynamic range of 2–9.52 mrad. Recording of OMT using the iTremor device takes ~3 seconds and is typically conducted in a seated position with eyes in the neutral position.

**Fig 2 pone.0313452.g002:**
[figure not shown]
iTremor ONE device.

#### Inertial sensors

Portable, light-weight inertial measurement units (Opals, APDM, USA) will be placed on the participant at various locations (i.e., feet, lower back, chest, wrists) using elasticated Velcro straps. These sensors contain accelerometer and gyroscope technology, have a high sampling rate and are small in size (~44mm x 50mm x 14mm (LxWxH)). The raw data collected from these is stored on the sensors and wirelessly streamed to APDM Mobility Lab, to provide automatic output of gait and balance outcomes. These outcomes include stride length, step time variability, gait speed, and trunk and arm range of motion. Turn characteristics are also recorded during walking.

#### Testing protocol

A schedule of enrolment and assessments is presented in Fig 1.

#### Step 1: Clinical recruitment

A member of the research team will provide the participant with the necessary oral and written explanations to obtain their signed/written informed consent before beginning the study. Participants will be invited to the clinical gait laboratory at Northumbria University, [name] Campus for the lab-based assessment.

*Diagnosis outcome*. Researchers and clinicians involved in the study will make note of the diagnostic outcome for those with suspected PD (i.e., either diagnosed with PD or not) provided by either Clinical or DATSCAN outcome, which will be obtained from the participant medical record and added to the secure participants database (i.e., PD; YES or NO).

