Neurological disease also significantly decreases OMT frequency when compared to healthy controls. For example in PD, a study reported a mean OMT frequency of 67.68Hz (Healthy range = 70 – 130Hz [29]). In another study focusing on OMT and idiopathic PD, authors observed two groups–an ON group and OFF group [20]. These were determined using the bradykinesia subsection of the Webster Scale [32]. A score of 0 or 1 was considered ON (n = 12), and a score of 2 or 3 was considered OFF (n = 10). The healthy controls in this study had a mean OMT frequency of 81.64Hz (SD = 6.10) and both PD ON, and PD OFF, groups exhibited significantly lower OMT frequencies of 73.78Hz (SD = 5.55) and 58.88Hz (SD = 10.35) respectively; the mean frequency of the OFF group was significantly lower than that of the ON group. This preliminary evidence suggests that People with PD have reduced OMT, thus supporting the need for more robust evidence.

PD related motor symptoms tend to only be noticed when there has been a ~80% depletion of striatal dopamine and so identification of the disease using OMT as an objective measure could benefit prognosis and likely help identify subtle changes in the early stages [33]. Observing OMT through multiple recordings in patients in an ON and OFF state could yield insight to individual responsiveness to dopaminergic medication. Exploring OMT as a biomarker for PD using accessible novel technology could facilitate an objective diagnosis and monitoring of the disease and it’s progression [24]. Overall, this presented protocol aims to examine OMT as a potential marker for PD and for disease monitoring. To achieve this, the following aims are outlined:

Analytical Validation: (1) Investigate the test-retest reliability of the iTremor ONE device in measuring OMT frequency (Hz) in People with PD; (2) Investigate the feasibility of measuring OMT using a hand-held device in a real-world clinical setting. This will cover the reliability and feasibility of OMT measurement in People with PD.

Clinical Validation: (1) Compare OMT frequency in People with PD and age-matched controls, and suspected PD patients; (2) Explore relationships between OMT measurement in People with PD and other clinically relevant outcomes (e.g., UPDRS); and (3) Examine the effect on OMT of dopaminergic medication in PD. This will cover known groups validity, convergent/divergent validity and response to a known intervention in People with PD.

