#### Statistical analysis

Statistical analysis will be undertaken using SPSS version 26 or more recent versions (SPPS, Inc. an IBM company). All statistical tests will be carried out at the 5% two-sided level of significance. Demographic characteristics and baseline data will be summarized using descriptive statistics, including means, standard deviations, median, minimum, maximum and inter-quartile ranges for continuous or ordinal data and percentages for categorical data. The descriptive statistics will be tabulated and presented graphically for clarity.

*Analytical validation aim I*. *Reliability*: To assess test, re-test reliability in PD, OMT frequency outcomes from the iTremor One device will be assessed on two separate home-based sessions and compared. Absolute agreement between sessions will be assessed using intra-class correlations (ICC2,1). ICCs will be interpreted as; poor <0.5, moderate 0.50–0.75, good 0.75–0.90 and excellent >0.90 [49]. Additionally, Bland-Altman graphs, with mean differences and limits of agreement will compare OMT between the two sessions, and Pearson’s correlations will also be used.

*Analytical validation aim II*. *Feasibility*: Feasibility outcomes will also be descriptively reported (e.g., number, percentages etc.) in relation to measurement of the OMT with the iTremor.

*Clinical validation aim I*. *Known groups validity*: To examine whether OMT can differentiate confirmed PD from suspected PD participants, we will use an analysis of variance (ANOVA), with group (confirmed PD vs suspected PD) as a between-subject factor. Although the study is not envisioned or powered to determine the efficacy of the OMT measurement for differential diagnosis of PD, we will further explore the difference in OMT between those with a positive diagnosis and those that did not receive a PD diagnosis. Specifically, receiver operating characteristic (ROC) curve analyses will be used to determine the relative sensitivity and specificity of OMT for differentiating the two patient groups (PD vs other diagnosis). This provides Area Under the Curve (AUC) which is a metric to evaluate the classifiers output quality.

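### The exploratory PD-versus-other-diagnosis ROC ignores whether suspected-PD participants have already started dopaminergic treatment when OMT is read, which may bias the AUC downward by an unknown amount

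*Protocol article*

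**What the plan says.** Under Step 1) Recruitment, "Participants will be seen in clinic by a Movements Disorders specialist at these sites where people are referred for suspected PD diagnosis". Under Step 1: Clinical recruitment, "Participants will be invited to the clinical gait laboratory at Northumbria University". The same section takes the diagnostic outcome of suspected cases from the medical record, on a clinical or a DaTSCAN basis, with no date relative to any other study event.

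The first OMT reading described for the suspected group is the one in Step 2: Laboratory assessment. The interview at that visit asks for current medications so that LEDD can be calculated. The text gives two intervals: about one month from Step 2 to Step 3a, and one week from Step 3a to Step 3b. The 12-hour withdrawal and the ON and OFF readings belong to Step 3a, which is for confirmed PD only.

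Under Statistical analysis, Clinical validation aim I, those with and without a positive diagnosis are compared by ROC, to obtain the "sensitivity and specificity of OMT for differentiating the two patient groups (PD vs other diagnosis"). I read this as an analysis within the suspected group. Covariates are named only as disease severity and cognitive function, for an ANCOVA. No stated analysis uses medication or LEDD. Clinical validation aim III examines whether OMT falls in the OFF state, and the Introduction cites a study in which "the mean frequency of the OFF group was significantly lower than that of the ON group".

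**The concern.** The suspected-group ROC is the analysis closest to the use of OMT at referral. For that purpose the reading should reflect the patient before diagnosis has led to treatment. As written, a patient can be diagnosed clinically at or soon after the clinic visit, start dopaminergic medication, and then have OMT read in the laboratory. Nothing in the text stops that reading from entering the ROC beside readings from untreated patients.

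On the protocol's own hypothesis, treatment raises OMT in PD. It would then move treated PD-positive participants toward those with another diagnosis and shrink the separation. The AUC would depend partly on how long the laboratory appointment took to arrange, and a better reference standard would not cure that. Disease severity as a covariate would not cure it either: it is offered for an ANCOVA, not for the ROC, and it is not treatment status.

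**Working it through.** **Nothing to reproduce.** The protocol gives no expected AUC, and "a formal sample size calculation was not conducted". The check is therefore of direction and possible scale.

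**Inputs from the Introduction (one cited study).** Controls: mean 81.64 Hz, SD 6.10. PD ON: 73.78 Hz, SD 5.55, n = 12. PD OFF: 58.88 Hz, SD 10.35, n = 10. ON meant a Webster bradykinesia score of 0 or 1, OFF a score of 2 or 3.

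**Input from Step 2) Lab assessment.** 30 suspected-PD participants.

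**Not given, so assumed over a range.** The share q of PD-positive participants treated at the reading: 0 to 100%. OMT in other diagnoses: mean 65 to 81.64 Hz, SD 6.10 to 10.35. PD cases among the 30: 15, 20 or 24. Participants with another diagnosis are taken as unaffected by dopaminergic treatment. Distributions are taken as normal.

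**Formula.** With low OMT indicating PD, AUC = Φ((mean_other − mean_PD) / √(SD_other² + SD_PD²)). With share q treated, AUC(q) = (1 − q) × AUC(untreated) + q × AUC(treated).

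**Illustration with other diagnoses like controls, untreated PD like OFF, treated PD like ON.**

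- Untreated: (81.64 − 58.88) / √(6.10² + 10.35²) = 22.76 / 12.01 = 1.89, so AUC = 0.971.
- Treated: (81.64 − 73.78) / √(6.10² + 5.55²) = 7.86 / 8.25 = 0.953, so AUC = 0.830.
- Example of a mixture, q = 25%: 0.75 × 0.971 + 0.25 × 0.830 = 0.936.

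**Varying OMT in other diagnoses.**

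| Other-diagnosis mean (SD) | 0% treated | 25% | 50% | 75% | 100% |
|---|---|---|---|---|---|
| 81.64 (6.10) | 0.971 | 0.936 | 0.900 | 0.865 | 0.830 |
| 81.64 (10.35) | 0.940 | 0.892 | 0.844 | 0.796 | 0.748 |
| 75 (6.10) | 0.910 | 0.822 | 0.734 | 0.647 | 0.559 |
| 73.78 (6.10) | 0.893 | 0.794 | 0.696 | 0.598 | 0.500 |
| 67.68 (6.10) | 0.768 | 0.633 | 0.499 | 0.364 | 0.230 |

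The AUC falls as the treated share rises in every combination tried. In the last row it passes below 0.5. If the direction of the ROC were chosen from the data, the reported AUC would be reflected above 0.5 and need not fall. The downward direction therefore requires low OMT to be fixed in advance as indicating PD.

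**Precision.** The Hanley-McNeil standard error of an AUC of 0.90 is 0.060 with 15 PD and 15 other, 0.056 with 20 and 10, and 0.058 with 24 and 6. In the first row of the table, the loss at 25% treated is 0.971 − 0.936 = 0.035, less than one standard error. The loss at 100% treated is 0.971 − 0.830 = 0.141, more than two.

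**What the ON and OFF labels can bear.** They describe bradykinesia scores in different patients, not drug intake. An untreated new referral with a score of 0 or 1 would have been placed in that study's ON group. If untreated participants resemble that group, the untreated AUC in the first row is already 0.830, and the 0.97 to 0.83 contrast says nothing about treatment.

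**The case against.** The strongest reply is that this is a silence in a condensed article. The Testing protocol section refers the schedule to Fig 1, which is not shown, and Secondary outcomes mentions a patient visit window without defining it. A window between clinic and laboratory may therefore exist. This stands: a reader might infer that the study has no such window, and the documents do not support that. They show only that the Step 1 and Step 2 text states none.

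Second, a reader might infer that patients diagnosed and treated at Step 1 will be analysed as suspected PD. No section says so. Suspected and confirmed PD are listed as separate groups at Step 2, and taking the outcome from the record fits a diagnosis still pending at enrolment. The text permits the scenario but does not plan it.

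Third, a reader might take it as established that medication raises OMT, and the AUC loss as 0.14. The drug effect is what aim III is meant to examine, and the cited contrast was not by drug intake. The Introduction also reports reduced OMT in neurological disease generally, so other diagnoses need not resemble controls. That participants with another diagnosis are not given dopaminergic medication is likewise an assumption.

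Fourth, the ROC is exploratory, the protocol says the study is not powered for differential diagnosis, and medications are already recorded, so treated participants can be identified. All true. This lowers the consequence but leaves the stated ROC pooling treated and untreated cases when the data to separate them are at hand.

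**Conclusion.** The point holds in conditional form. Readings in the suspected group may be taken after diagnosis and after treatment has begun, and the stated ROC makes no distinction. The AUC is biased downward if three things are true: some PD-positive participants are on dopaminergic medication at the Step 2 reading; OMT is lower off medication, as the protocol hypothesises; and low OMT is fixed beforehand as indicating PD. It also assumes that treatment does not shift the other-diagnosis group in the same way.

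The size cannot be stated. The treated share and OMT in other diagnoses are not given, and the cited ON and OFF groups stand in only loosely for treated and untreated early PD. The range of 0.97 to 0.83 shows that the effect could matter, and is not an estimate. The consequence is confined to one exploratory analysis. The point does not touch the ON/OFF comparison or the test-retest work.

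**What to change.** In the suspected-PD group, use the Step 2 medication interview to classify each participant as on or not on dopaminergic medication at the OMT reading, and record the date of diagnosis relative to that reading. Run the PD-versus-other-diagnosis ROC in those untreated at the reading, with low OMT fixed as indicating PD. Report the all-participant ROC beside it, and the treated participants separately. If Fig 1 or the full protocol already sets a window from clinic to laboratory, state it in the text.

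The medication data are already collected. The additions are one date and one analysis-set rule. The downside is a smaller and less precise ROC set from at most 30 participants. The untreated may also be a less clear-cut subset of cases, which is a further reason to show the all-participant result.

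Taking the reading at the clinic is not needed. Study setting lists only the laboratory and the home as collection sites, so it would add a procedure to a study already recruiting. Nothing here changes or delays care.

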#### Step 2: Laboratory assessment (Suspected PD, confirmed PD and HC groups)

*Demographics*. The participant will then be interviewed by a member of the study team. The interview will include questions regarding education level, falls history, current medications, history of head injury, activity level, and side dominance as well as basic demographics such as age and gender. We will ask participants for their medications currently used (so that we can calculate the levodopa equivalent daily dosage (LEDD) [37, 38].

*Cognitive assessment*: Participants will also undergo a battery of cognitive, motor, and visual assessments. The cognitive assessments should last around 30 minutes and consist of a series of pen and paper tasks which the participants will be guided through by a member of the research team. Global cognition is assessed using the Montreal Cognitive Assessment (MoCA) [39]. Benton’s Judgement of Line Orientation test assesses visuospatial skill (JLO) [40]. The trail making test of visual attention (TMT A and B) is used to assess executive functioning [41] as well as Royall’s Clock Drawing task (CLOX 1&2) [42]. Forward digit span [43] is used as a measure of working memory. Participants will also complete a series of computerised tests to assess attention using a button pressing task. This attention battery is a valid means of testing attention and has been implemented in previous studies involving People with PD [44].

*Visual assessment*: The visual assessments are conducted binocularly before using an eye occluder to measure for the left and right eyes independently. The visual assessments should take 10 minutes to complete.

*Visual acuity—LogMAR*. This test is a simple visual test to assess participants ability to read at a distance. The Logarithm of the Minimal Angle of Resolution (LogMAR) is used as a standardised binocular measure. Participants are seated at a 4-meter distance from the chart and asked to read the letters aloud from left to right starting at the top left. The participant is stopped if two incorrect letters are given. LogMAR is calculated using the following formula: LogMAR = (score of the line before termination)–(0.02 x the number of errors) + (0.02 x correct answers before terminal line). A LogMAR score of 0.00 is equivalent to 6/6 (20/20) vision. The LogMAR charts are scored by letter instead of row making them a more precise measure of visual acuity.

*Contrast sensitivity—LogCS*. This is measured using the Mars CS sheets. These sheets consist of 48 Latin letters of uniform height, and the contrast from the white background decreases with each letter. The participant is seated 50 centimetres (cm) from the sheet and again reads from left to right, starting at the top left. Errors are recorded by the investigator and the test is terminated when two consecutive errors are made. LogCS is calculated using the following formula: (value of final correct letter before stopping)–(number of errors prior to stopping x 0.04). Again, answers are recorded for binocular vision then for left, and right eyes independently using an occluder.

*Motor assessment*: To assess disease severity and motor symptoms in People with PD, the Movement Disorder Society Unified Parkinson’s disease Rating scale part III (UPDRS-III) is used [45]. The motor assessments should take around 30 minutes. The UPDRS will be conducted first before setting up the sensors for the balance and gait assessments. People with PD will be categorised based on their disease severity using the Hoehn and Yahr scale (H&Y) [46]. This is a widely used clinical scale for defining motor symptoms in PD, which is a part of the UPDRS-III. It consists of five stages–stage I, unilateral symptoms with no functional disability, to stage V, complete disability and patient is bedbound. This scale is easily applicable and widely used to assess PD. There will also be a short self-report questionnaire on freezing of gait, using the new Freezing of Gait Questionnaire (nFOGQ) [47]. In addition, the Falls Efficacy Scale–International (FES-I) [48], a self-report evaluation to assess fear of falling will be completed.

*Balance*. Participants will stand for several periods of up to 2 minutes under different conditions (i.e., eyes open, eyes closed, and on a foam block with eyes open, and closed) with balance measured via mobile inertial measurement units (APDM, USA). These sensors are located at the wrists, feet, chest, and lower back to measure postural sway.

*Gait*. Participants will walk back and forth over a marked out 10m distance for several periods of up to 2 minutes under different conditions (i.e., normal walking and walking while repeating numbers) with gait measured via mobile inertial measurement units (APDM, USA). Turns are included in this walking sequence. These sensors are located at the wrists, feet, chest, and lower back.

*OMT assessment*: OMT will be measured using the iTremor Device (Fig 2). The participant will be asked to sit comfortably with their head resting on the chair’s headrest. If the participant wears glasses or contact lenses they will be asked to remove these for the duration of the recordings. The participant is asked to look straight ahead at a target on the wall without straining their eyes for a ~3 second period. The participant remains relaxed whilst the researcher positions the device, gently leaning on the participants cheek and brow bone. The guide light is lined up from the side of the eye with the scleral surface of the eye and the researcher cues the participant to not blink before pressing the trigger on the device. An optical beam is emitted from a diode in the device at low power with light scattered back from the eye and reflected back into the device and passed to a video imaging sensor. Three readings will be taken for each eye. If the participant blinks, the reading is just repeated. Unwanted eye movements or blinks are filtered out in raw data post-processing. A frequency will be shown on the device’s display screen in Hz. This is repeated three times for each eye independently.

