#### Secondary outcomes

Secondary outcomes for the study include cognition, visual function, motor symptoms (UPDRS-III), gait and balance. Diagnosis will also be recorded from the medical records for Step 1; specifically positive or negative PD diagnosis (i.e., PD; YES or NO).

Within clinic feasibility outcomes will include the following:

The number of adverse events (mild, moderate or severe) during the OMT measurement, if any, are recorded in an incident log. The total number will be assessed and compared.

The number of OMT measurement device issues (e.g., breakdowns, inability to record OMT etc.) and success of data recording (percentage of failed recordings / missing data). This may be device related or due to other factors such as environmental or patient specific difficulties.

Compliance adherence in terms of the number of completed OMT recordings from patients and their timeliness in terms of collection in the patient visit window.

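### The printed LogMAR formula has both signs reversed and does not define which letters are counted, so following it mis-scores visual acuity, one part of a secondary outcome.

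*Protocol article*

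**What the plan says.** The visual acuity paragraph under Step 2 (Laboratory assessment) of the protocol article states:

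- **Scale:** "The Logarithm of the Minimal Angle of Resolution (LogMAR) is used as a standardised binocular measure".
- **Anchor:** "A LogMAR score of 0.00 is equivalent to 6/6 (20/20) vision".
- **Stopping rule:** "The participant is stopped if two incorrect letters are given".
- **Formula:** "LogMAR = (score of the line before termination)–(0.02 x the number of errors) + (0.02 x correct answers before terminal line"). The part at issue is the two letter terms, –("0.02 x the number of errors) + (0.02 x correct answers before terminal line").
- **Reason for scoring this way:** "The LogMAR charts are scored by letter instead of row making them a more precise measure of visual acuity".

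The contrast sensitivity paragraph that follows gives a separate formula for LogCS: ("value of final correct letter before stopping)–(number of errors prior to stopping x 0.04").

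Acuity belongs to visual function, which the Secondary outcomes section lists: "Secondary outcomes for the study include cognition, visual function, motor symptoms (UPDRS-III), gait and balance". No other section restates or corrects the LogMAR formula.

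**The concern.** The two adjustments run against the scale. If LogMAR rises as vision worsens, a missed letter should raise the score and an extra letter read should lower it. The formula does the reverse on both terms. Subtracting errors suits a scale on which higher is better. That is the case for LogCS, where the protocol's formula has the right direction.

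The wording of the counts is a second problem. It does not say whether errors are those on completed lines, those on the line where reading stops, or both. The correct answers are described as lying before the terminal line, although an adjustment for extra letters needs those read on that line.

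At stake is the accuracy of the acuity values, taken for both eyes together and for each eye separately in all three groups. The discrepancy depends on each participant's letter counts. It is therefore not a constant shift that would drop out of a comparison, and it reverses the ranking of participants who stop on the same line with the same number of earlier errors.

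**Working it through.** **Inputs from the protocol.** 0.02 per letter, both signs, the 6/6 anchor at 0.00, and the two-error stop.

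**Assumptions not in the protocol.** Five letters per line and 0.10 LogMAR per line (consistent with 5 x 0.02 = 0.10), a top line of 1.0, and a stop at two errors in total.

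**Step 1: direction of the scale.** Take the angle at 6/6 as one unit, so log10(1) = 0.00, as the protocol says. Half that angle gives log10(0.5) = −0.30, and twice that angle gives log10(2) = +0.30. Higher is worse. The protocol does not say this in words, but its definition fixes it.

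**Step 2: is the dash a minus sign?** Yes. The next term is joined by a plus, and the LogCS formula uses the same dash as a minus.

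**Step 3: printed formula against by-letter scoring.** Let L be the value of the last line before the terminal line, E the errors up to and including that line, and C the letters read correctly on the terminal line.

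- Printed: L − 0.02E + 0.02C
- By letter: 1.1 − 0.02 x (total letters correct), which equals L + 0.02E − 0.02C
- Printed minus by letter: 0.04 x (C − E)

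For L = 0.10, ten lines (1.0 down to 0.1) hold 50 letters:

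| E | C | Printed | By letter | Difference |
|---|---|---|---|---|
| 0 | 0 | 0.10 | 0.10 | 0.00 |
| 0 | 1 | 0.12 | 0.08 | +0.04 |
| 0 | 2 | 0.14 | 0.06 | +0.08 |
| 0 | 3 | 0.16 | 0.04 | +0.12 |
| 1 | 0 | 0.08 | 0.12 | −0.04 |
| 1 | 1 | 0.10 | 0.10 | 0.00 |
| 1 | 4 | 0.16 | 0.04 | +0.12 |

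Check of the fourth row: 53 letters correct gives 1.1 − 0.02 x 53 = 0.04.

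**Step 4: which cases can occur.** With a stop at the second error in total, E is 0 or 1.

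- E = 0: both errors fall on the terminal line, so C is 0 to 3 and the difference is 0.00 to +0.12.
- E = 1: one error falls on the terminal line, so C is 0 to 4 and the difference is −0.04 to +0.12.

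The overall range is −0.04 to +0.12. If the stop instead means two errors on one line, C is at most 3, so the upper end stays at +0.12. Earlier lines could then each hold one miss, and the lower end would extend by 0.04 for each.

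**Step 5: other readings of the counts.**

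- *Errors counted on the terminal line only (L = 0.10, two errors, three correct, none earlier).* Printed: 0.10 − 0.04 + 0.06 = 0.12. By letter: 0.04. Reversing the signs alone gives 0.10 + 0.04 − 0.06 = 0.08, which is still wrong because letters not read on the terminal line are already uncredited.
- *Terminal line (0.00) as the reference, errors only, two errors.* Printed direction: −0.04. By letter: +0.04.
- *Correct answers taken literally as all letters before the terminal line (50).* Printed: 0.10 + 1.00 = 1.10. With signs reversed: 0.10 − 1.00 = −0.90. Neither is usable.

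No reading rescues the printed signs, and the third shows that the counts need defining too.

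**Step 6: comparison with ignoring letters.** If d is the net letter adjustment, the by-letter score is L − d, the row score is L and the printed score is L + d. The row score misses by d and the printed score by 2d. In the example the row score (0.10) is off by 0.06 and the printed score (0.16) by 0.12.

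**The case against.** The strongest reply is about consequence. Acuity is one part of one of five secondary domains, alongside contrast sensitivity. The primary outcome is OMT frequency. The eligibility criteria set no LogMAR cut-off, and the covariates named for the ANCOVA are disease severity and cognitive function. All of this stands and limits the severity.

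Three stronger readings are tempting, and the protocol does not support them.

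- **That the acuity data already collected are wrong.** The article shows a printed formula, not the scoring sheet. A swap of two operators in the write-up would produce the same text. Recruitment began in June 2023, so scores may exist, but nothing shows how they were computed.
- **That group comparisons and OMT–vision correlations would be corrupted.** The Statistical analysis section names no group test of vision. For correlations it gives UPDRS and MoCA as examples. Vision could fall under the open-ended wording, but no such analysis is stated.
- **That the error spans −0.08 to +0.16, or reaches 0.20.** An error of +0.16 with E = 0 needs four of five letters correct on the terminal line, which leaves only one error, so the reader has not been stopped. A −0.08 needs two earlier errors, which would already have ended the test under a total count. A 0.20 needs five correct letters on the terminal line, which is then not a terminal line.

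The sign error itself has no good answer: the definition of the scale sits in the same paragraph as the formula. Checking the 6/6 anchor would not reveal it, because the printed and by-letter scores agree whenever E = C, including 0 and 0.

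**Conclusion.** The point holds. As printed, the formula rewards errors and penalises correct letters on a scale where higher is worse, and it does not define its counts. The mis-scoring is 0.04 LogMAR per net letter. It runs from −0.04 to +0.12 if lines have five letters, errors are counted on earlier lines, correct letters are counted on the terminal line, and reading stops at two errors in total. The upper end exceeds one full line. The sign finding needs none of these assumptions; only the range does.

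The effect is confined to visual acuity. It does not touch OMT frequency or any analysis the protocol names explicitly. Whether recorded values are affected depends on the scoring sheet, which is not shown.

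**What to change.** Replace the formula with:

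LogMAR = (value of the last line before the terminal line) + (0.02 x letters missed on lines up to and including that line) − (0.02 x letters read correctly on the terminal line).

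Add that errors on the terminal line are not counted again, and say whether the two-error stop is a total or applies within one line. With these definitions the formula matched direct by-letter scoring in all 12 combinations tried (0 or 1 earlier error, 0 to 5 letters correct on the next line).

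Then check which formula the scoring sheet actually uses. Rescore only if the printed one was applied, working from letter-level responses where these were recorded; the Data processing section says a hard copy of the assessment is kept. If the sheet was already right, a correction to the published text is enough.

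The cost is a few lines of text and one check of the sheet, plus re-running the acuity scores if needed. No new assessments are required.
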